## Abstract

**Background:**

Despite international efforts to arrest increasing rates of overweight and obesity, many population strategies have neglected young adults as a target group. Young adults are at high risk for unhealthy weight gain which tends to persist throughout adulthood with associated chronic disease health risks.

**Methods/design:**

TXT2BFiT is a nine month two-arm parallel-group randomized controlled trial aimed at improving weight management and weight-related dietary and physical activity behaviors among young adults. Participants are recruited via general practice (primary medical care) clinics in Sydney, New South Wales, Australia. All participants receive a mailed resource outlining national physical activity and dietary guidelines and access to the study website. Additional resources accessible to the intervention arm via the study website include Smartphone mobile applications, printable handouts, an interactive healthy weight tracker chart, and a community blog. The study consists of two phases: (1) Intensive phase (weeks 1 to 12): the control arm receives four short message service (SMS) text messages; the intervention arm receives eight SMS messages/week tailored to their baseline stage-of-change, one Email/week, and personalized coaching calls during weeks 0, 2, 5, 8, and 11; and (2) Maintenance phase (weeks 14 to 36): the intervention arm receives one SMS message/month, one Email/month and booster coaching calls during months 5 and 8. A sample of N = 354 (177 per arm) is required to detect differences in primary outcomes: body weight (kg) and body mass index (kg/m^2^), and secondary outcomes: physical activity, sitting time, intake of specific foods, beverages and nutrients, stage-of-change, self-efficacy and participant well-being, at three and nine months. Program reach, costs, implementation and participant engagement will also be assessed.

**Discussion:**

This mobile phone based program addresses an important gap in obesity prevention efforts to date. The method of intervention delivery is via platforms that are highly accessible and appropriate for this population group. If effective, further translational research will be required to assess how this program might operate in the broader community.

**Trial registration:**

Australian New Zealand Clinical Trials Registry ACTRN12612000924853

## Background

Globally, population body mass index (BMI) has been shown to have progressively increased since the 1980s, placing escalating burdens on public health and requiring urgent intervention and policies to reverse this trend [1]. Despite concerted international efforts to arrest increasing rates of overweight and obesity, most strategies have targeted middle-aged adults, children and adolescents [2], while young adults have been largely neglected. A generational effect has arisen, whereby cohorts born between 1960 and 1975 are at greater risk for becoming overweight or obese than previous generations [3-5]. Risk of overweight and obesity has also increased with age up until the mid-50s to mid-60s, with variations between the genders [3,5]. The most rapid weight gain in the life-course has been observed during the early to mid-twenties [6], a life-stage more commonly termed ‘young adulthood’ or ‘emerging adulthood’ [7]. Weight gain during this life-stage has been associated with an increased risk of developing chronic disease risk factors [8-10], and with endometrial cancer [11].

A number of important lifestyle risk factors have been associated with weight gain during this life-stage. Namely, a decline in physical activity [12], an increase in sedentary behavior [13], frequent consumption of fast-food (energy-dense take-away meals) and sugar-sweetened beverages (SSB) [14,15], as well as higher total energy and fat intakes [16]. Another potential risk factor is the inadequate fruit and vegetable intake evident among young adults [17], given the ‘hypo-energetic’ nature of fruit and vegetables and evidence indicating a reduced risk of weight gain with increasing intake [18].

Despite the clear risk for weight gain during young adulthood, evidence to inform effective interventions for this population is lacking [19]. Easy access to treatment has been identified as important in this age group [20], and hence mobile phone-based interventions hold promise for delivering interventions with potentially low resource intensity and wide population reach. At the end of 2011, for every 100 persons there were 86 mobile phone subscriptions globally (122 in developed countries) and 16 mobile broadband subscriptions (51 in developed countries) [21]. In 2012, 74% of 25 to 34 year-olds owned a ‘Smartphone’, compared with 56% of those aged over 13 years [22]. Furthermore, 18 to 29 year-olds send/receive an average of 88 SMS text messages each day - more than triple the volume sent by 30 to 49 year-olds [23].

A pilot randomized controlled trial (RCT) was conducted in the latter half of 2011, with young adults recruited through the tertiary education setting (unpublished). Process findings from this research revealed that the young adults studied preferred set targets for their body weight, with regular weight monitoring, personalized regular contact for accountability, support with planning meals and work/rest/activity schedules, faster operating time of and motivation/reminders to use Smartphone applications, and to receive text messages outside of morning hours. Based on these findings, the program and materials were refined to develop the TXT2BFiT program. This paper reports the protocol for a RCT aimed at (1) testing the efficacy of the TXT2BFiT program by comparing changes in body weight and selected dietary, physical activity and sedentary behaviors among young adults aged 18 to 35 years with changes in a control group, and (2) evaluating program reach, costs, implementation and participant engagement to inform the potential future translation of the program into the broader community.

## Methods/design

Materials and methods of the TXT2BFiT nine month (36 week) parallel-group RCT were approved by the University of Sydney Human Research Ethics Committee in September 2012 (Approval number 15226). The trial is registered with the Australian New Zealand Clinical Trials Registry (ACTRN 12612000924853). It is hypothesized that the tailored TXT2BFiT program will be more effective in improving young adults’ diets, physical activity and weight management, over nine months, compared with controls.

### Participants

Participants are patients of general practice (primary medical care) clinics in the Sydney area, New South Wales, Australia. Eligibility criteria for patients to participate in the study are presented in Table 1. Adults aged 18 to 35 years are selected to include both emerging adulthood (18 to 25 years) and the years until middle-age [3].

**Table 1 T1:** Participant eligibility criteria for participation in the TXT2BFiT trial

**Inclusion criteria**	
1	Body mass index 25.0 to 31.9 kg/m^2 ^or 23.0 to 24.9 kg/m^2^ with reported weight gain > 2 kg over past 12 months.
2	Aged 18 to 35 years.
3	Fruit intake < two serves/day and/or vegetable intake < five serves/day and/or sugar sweetened beverage intake ≥ 1 L/week and/or energy-dense take-away meals > once/week and/or moderate intensity physical activity < 60 minutes/day.
4	Has mobile phone capable of receiving text messages and access to the Internet at least once a week.
**Exclusion criteria**	
1	Pregnant or planning to fall pregnant within the next nine months.
2	Enrolled in an alternate weight loss program.
3	Has lost > 10 kg voluntarily in the past three months.
4	Taking medications that have caused > 2 kg weight gain.
5	Medical condition that precludes following dietary or physical recommendations.
6	History of disordered eating.
7	Does not speak English.

### Procedure

Australian primary health care services were re-organized in July 2011 into independent entities called ‘Medicare Locals’, which are responsible for coordinating primary health care over a specified geographic area. From the Medicare Local, fax and Email invitations are sent to general practitioners (GPs) within the area to partner in the recruitment of patients into the study. GPs returning their expression of interest are then contacted to arrange a time and date for the researchers to attend their practice clinic and to conduct an audit of their electronic patient database in order to identify suitable participants, that is, patients aged 18 to 35 years who have been seen by the GP in the prior 12 months. These patients are mailed a letter from the GP inviting them to participate in the research, along with a consent form and further information about the study. A maximum of 500 letters are sent from each general practice clinic. If more than 500 patients are identified, the first 500 patients are randomly selected. The invitation letter directs prospective participants to an online survey to screen for eligibility criteria (Table 1). Questions in the screening survey are structured such that ineligible patients are redirected to a national social marketing website for healthy eating and physical activity promotion. Eligible patients reaching the end of the survey are able to nominate dates and times to attend an appointment with their GP at no cost to the patient. This 10 minute appointment is then booked for the patient and details of the appointment sent to the patient in a confirmatory short message service (SMS) text message.

At each appointment, the GP measures the patient’s weight and height and obtains the patient’s informed consent to participate in the trial by collecting their signed consent form. Signed consent forms are then faxed back to the researchers with the patient’s anthropometric data to confirm eligibility on the basis of their BMI and to enroll the patient in the trial. Enrolled patients are then randomized to the intervention or control arm by one of the researchers and allocated their treatment by another researcher by way of an introductory phone call (control participants) or a coaching call (intervention participants) provided in week 0. Figure 1 provides a diagrammatic summary of participant enrollment, randomization, assessment, and allocated interventions (intervention and control) with associated time line. While participants are aware of another arm to the trial, every attempt is made to ensure that the nature of this other arm is not revealed.

**Figure 1 F1:**
[figure not shown]
Diagrammatic summary of participant enrollment, randomization, assessment, allocated interventions, and associated time line.

### Interventions

Control participants receive a mailed two-page handout summarizing the Australian national dietary and physical activity guidelines [24,25], an introductory call (week 0) to introduce the program (no coaching given), four SMS text messages (one every three weeks during weeks 1 to 12) that re-iterate information in the handout, and limited access to the TXT2BFiT website, that is, electronic versions of the two-page handout, consent form and study information statement, general information about the study and contact information. Intervention participants are mailed an eighteen-page booklet containing the two-page control handout, as well as sample meal plans, recommendations for daily servings from the core food groups with example serving sizes [25], and information about the four target behaviors addressed by the program: physical activity and sedentary behavior, intake of fruit and vegetables, intake of energy-dense take-away meals, and SSB intake, in conjunction with the TXT2BFiT mobile phone-based program.

#### TXT2BFiT program

This tailored program consists of SMS text messages, Emails, Smartphone mobile applications, a study website and personalized coaching calls (Figure 1). The program is grounded on processes-of-change theory [26], supported by self-monitoring, motivational interviewing and goal setting [27,28]. Through its various intervention components, the TXT2BFiT program consistently encourages participants to (1) consume five servings of vegetables and two servings of fruit per day, in line with the national dietary recommendations [25]; (2) limit energy-dense take-away meals to once per week or less [15]; (3) limit SSB to less than one liter per week [14]; (4) perform 60 minutes or more of moderate-intensity physical activity most days of the week (preferably daily), as evidence indicates that young adults are likely to require physical activity levels exceeding national guidelines to a level of approximately 45 to 60 minutes per day or 1.7 PAL (physical activity level; ratio of total to basal energy expenditure) to prevent weight gain [12,29].

### Study website

Each participant is provided with a unique login for the study website, to differentiate between the resources available to intervention and control subjects [30]. Throughout the nine month intervention, participants are able to access seven printable handouts to support physical activity, meal planning and selecting healthier foods and drinks when eating away from home; an interactive healthy weight tracker chart with green, yellow and red bars to indicate healthy, overweight and obesity, respectively, for self-monitoring changes in their BMI [31]; four Smartphone mobile applications developed to assist with forming self-monitoring skills for each target behavior [32]; and a community blog on which participants may post comments or questions to the researchers and communicate with other intervention participants.

### SMS text messages

Text messages are framed on the ten processes-of-change which define how one transitions from one stage-of-change to the next in the transtheoretical model for health behavior change [26]. Messages sent in week one are framed around the first process-of-change consciousness raising, which is aimed at ‘increasing information about self and problem…’ [26] in order to inform participants about how the target behaviors increase the risk for weight gain and recommendations for changing these behaviors to avoid weight gain. Subsequent text messages sent during the remaining 11 weeks of the intensive phase are tailored to the processes-of-change evident to be used in transitioning to action or maintenance from the participants’ baseline stage-of-change; that is, pre-contemplation (not thinking about change), intention (contemplation/preparation) or action (action/maintenance) [33-37]. For example, a greater proportion of text messages sent to participants in preparation for changing their fruit and vegetable intake are framed on self-reevaluation and helping relationships (that is, obtaining social support), as these processes are identified in the literature as assisting transition from intention to action for fruit and vegetable intake [34,36]. Fruit and vegetable messages coupled with replacing energy-dense foods, such as confectionery, crisps and energy-dense take-away foods with fruit or vegetables to promote a reduction in total energy intake for weight management [38]. Text messages are also tailored to gender, given the different motivators behind health behavior change experienced by men and women. For example, females may perceive a lack of exercise as conducive to weight gain, while males perceive this as conducive to weight loss (that is, muscle mass loss) [39]. Socio-cultural norms for young adults were also considered in developing the text messages. For example, young adults tend to use SSB as a mixer with alcohol and hence messages were developed to address moderating SSB consumption with alcohol [40]. Also considered were young adults’ perceived benefits and barriers to performing the desired behaviors, for example, lack of time [39], which was addressed by communicating convenient alternatives for healthy eating and physical activity. All text messages were sent using a two-way text messaging platform from a major commercial SMS service provider. Table 2 provides example text messages framed according to gender and processes-of-change consciousness raising and counter-conditioning (that is, ‘substituting alternatives for problem behaviors…’) [26].

**Table 2 T2:** **Example mobile text messages framed according to gender and the processes-of-change *****consciousness raising *****and *****counter-conditioning***

**Process-of-change**	**Gender**	**Fruit and vegetables**	**Physical activity**	**Sugar-sweetened beverages**	**Energy dense take-away meals**
**Consciousness raising**	***Males***	Fruit & Veg R high in fiber 2 keep U full & R low in fat. Stay Fit, without going hungry. Chicken breast & salad roll no butter (only 6 g Fat).	FACT: Physical activity improves mental alertness, reduces stress & depression & keeps U feeling energized. Plan 30mins of activity 4 tomorrow.	FACT: Sugary drinks give us a fast hit of energy. But just 1 hr after a sugary drink ur blood sugar levels drop affecting physical & mental performance.	FACT: Eating takeaway more than twice a week increases ur risk of gaining body fat & abdominal obesity (beer belly). TXT how many times a week U have takeaway.
	***Females***	FACT: Including Fruit & Veg makes it much easier 2 achieve & maintain a healthy weight. TXT how many Fruit & Veg U usually eat a day.	FACT: Women carrying excess weight R @ HIGH risk 4 further weight gain. Being active will STOP this weight gain. TXT the mins of activity U do in a week.	FACT: Sugary drinks give us a rush of energy from all the kilojoules. But just 1 hr after a sugary drink ur blood sugar levels drop causing U 2 feel tired & low.	FACT: Many takeaways contain over 1/2 ur daily kilojoules (kJ) needs. Check the kJ of ur meals: eTIYP mobile app @ http://txt2bfit.com/mobile-apps
**Counter-conditioning**	***Males***	Home late? U need an emergency kit: Pantry (tin corn, tomatoes, baked beans, tuna). Freezer (grainy bread, packet mixed Veg). Fridge (low fat cheese, eggs).	How many hrs do U spend online? Use ur mobile so U can walk while on the net. Avoid sitting by using stairs, walk don’t drive, cycle 2 work/study :-)	Do U use sugary drinks as a mixer 4 alcohol? U don’t have 2 miss out, just choose a diet (sugar free) drink as ur mixer.	THAI TIP: Avoid those fatty entrees. Try a hot chicken/beef/tofu salad with rice. Visit http://txt2bfit.com 4 more takeaway tips :-)
	***Females***	Always eating breakfast on the go? Choose a breakfast cereal with >5 g fibre/100 g & <20 g sugar/100 g, top with banana, strawberries & skim/low fat milk.	Eaten 2 much? Walk it off. 30mins tomorrow morning. Next time use a smaller plate, eat earlier & walk after. TXT ‘OK’ if U read this.	Craving guilt free enjoyment? Quench ur thirst with water. Add a twist of lemon 4 a hit of VitaminC. Leave the lemon in your bottle & fill up 4 FREE.	Planning takeout & TV tonight? Walk 2 the shops instead: frozen stir-fry vegies, beef OR tofu, soy sauce, garlic & rice.

### Coaching calls

The aims of the coaching calls are to set personalized goals with participants, educate them on healthy eating and physical activity for weight management, address personal barriers to behavior change, maintain motivation and notify participants of, and encourage them to use, the additional program materials available. At each coaching call, participants are asked about their current body weight, diet and physical activity in order to set goals to be achieved by their next coaching call (approximately two or three weeks), as setting proximal dietary and weight-related goals may be more effective than distal (long-term) goals [27]. During each call, one goal is set with participants for their body weight and between one and three goals for their diet or physical activity (around the target behaviors or other weight-related aspect of their diet or physical activity). Coaching calls are delivered by a dietitian with regular quality checks by an external researcher listening to calls in order to ensure adherence to pre-specified procedures.

### Emails

Emails sent to intervention participants act as reminders to use the program materials available, and provide an additional source of education on healthy eating, physical activity, goal setting and self-monitoring behaviors.

### Outcome measures

Measurements are taken at baseline (T0), three months (T1, week 13) and nine months (T2, week 37) (Figure 1). At each time point, participants complete an online survey to assess weight; height; stage-of-change; well-being; intake of fruit, vegetables, energy dense take-away meals, SSB, and water; knowledge of fruit and vegetable recommendations; physical activity; sitting time; and self-efficacy.

#### Demographics

At baseline, all participants are asked their age, gender, ethnicity (language spoken at home [41]), postcode (for categorizing socio-economic status [42]), education level [41], living arrangement, income bracket [41], and number of hours spent in work or study per week.

#### Primary outcomes

Body weight is measured to the nearest 0.1 kg at baseline by the GP and again after three months by study personnel blinded to participant allocation using WHO protocols [31]. Self-reported weight is collected at baseline, three months and nine months via an online survey. BMI is calculated as weight (kg) / [height (metres)^2^ at baseline, three months and nine months.

#### Secondary outcomes

Frequency of consuming specific foods and drinks (fruit, vegetables, energy-dense take-away meals, SSB, and water) is assessed using short dietary questions [43,44]. Knowledge of fruit and vegetable recommendations is assessed using the question ‘What do you think is the recommended number of serves of (fruit/vegetables) that should be eaten in a day?’ adapted from Pollard *et al*. [45]. Multiple choice response options are ‘one serve a day’, ‘two or three serves a day’, ‘four or five serves a day’ and ‘six or more serves a day’ for fruit and ‘one or two serves a day’, ‘three or four serves a day’ and ‘five or more serves a day’ for vegetables. Intake of specific nutrients (energy, protein, total fat, saturated fat, carbohydrate, sugars, dietary fiber, and alcohol) is assessed using an online food frequency questionnaire, the Dietary Questionnaire for Epidemiological Studies version 2 (DQES v2), administered at baseline and three months [46]. Stage-of-change for the target dietary behaviors (fruit, vegetables, energy-dense take-away meals and SSB) is assessed by firstly measuring the target behavior, for example, serves of vegetables eaten per day. Participants reporting the desired behavior (that is, vegetable serves five or more per day; fruit serves two or three per day; energy-dense take-away meals ≤ once per week; SSB < 1 L per week) are directed to the question: ‘Have you been eating/drinking this amount of (behavior) for more than six months?’ to classify them as being in either action (performing the desired behavior for ≤ six months) or maintenance (performing the desired behavior for > six months). Participants not performing the desired behavior are asked: ‘Are you thinking about eating/drinking more/less (behavior) sometime in the next six months?’ to classify those in contemplation/preparation (intent on changing in ≤ six months) or pre-contemplation (not intent on changing in ≤ six months). Participants intent on changing in ≤ six months are further asked: ‘Are you planning to eat/drink more/less (behavior) sometime in the next month?’ to discriminate between those in preparation (intent on changing in ≤ one month) or contemplation (not intent on changing in ≤ one month).

Physical activity and time spent sitting in the previous seven days are self-reported using the International Physical Activity Questionnaire [47], and the domain specific sitting time questionnaire [48], respectively. Stage-of-change for physical activity behavior is assessed using the question: ‘Thinking about the last two weeks, on average, did you do physical activity for at least 60 minutes each day?*’* adapted from Marcus *et al*. [49], with response options ‘Yes, and I have been doing this for more than six months’ (maintenance), ‘Yes, but I have been doing this for less than six months’ (action), ‘No, but I intend to in the next 30 days’ (preparation), ‘No, but I intend to in the next six months’ (contemplation), ‘No, and I do not intend to in the next six months’ (pre-contemplation).

Self-efficacy in performing each of the target behaviors is assessed with the question ‘How confident are you that you can…(perform the target behavior, for example, eat at least five serves of vegetables each day (one serve = one cup salad OR half a cup cooked vegetables))?’ with response options on a four-point Likert scale from ‘Not at all confident’ to ‘Very confident’ adapted from the Project-Eat II survey for young adults [50]. Well-being is assessed using the WHO-5 well-being index which assesses five items of subjective well-being in the past two weeks on a six-point Likert scale ranging from ‘All of the time’ to ‘At no time’ [51].

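### The fruit stage-of-change rule stops at three serves a day, so a participant eating four or more cannot be scored as in action or maintenance

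*Protocol article*

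**What the plan says.** Stage-of-change is listed as a secondary outcome in the Abstract. For the dietary behaviours, the Secondary outcomes section first measures intake and then branches. Those reporting the desired behaviour, for fruit and vegetables "vegetable serves five or more per day; fruit serves two or three per day", are asked how long they have kept it up, which places them in action or maintenance. The other branch opens with "Participants not performing the desired behavior are asked" and asks about intentions. It leads only to pre-contemplation, contemplation or preparation.

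Other statements bear on the fruit rule:

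- **TXT2BFiT program:** participants are encouraged to "consume five servings of vegetables and two servings of fruit per day".
- **Table 1, inclusion criterion 3:** the dietary deficits begin with "Fruit intake < two serves/day and/or vegetable intake < five serves/day".
- **Background:** a lower risk of weight gain is cited as fruit and vegetable intake rises.
- **SMS text messages:** messages after week 1 are tailored to baseline stage, and fruit or vegetables are promoted as replacements for energy-dense foods.

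For activity, the program goal is to "perform 60 minutes or more of moderate-intensity physical activity most days of the week (preferably daily"). The stage item asks: "Thinking about the last two weeks, on average, did you do physical activity for at least 60 minutes each day".

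**The concern.** A stage-of-change measure should place people who have reached the target behaviour above those who have not. The fruit rule does this up to three serves and then stops. A participant who has gone furthest in the promoted direction is sent to the branch meant for people who have not yet changed.

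Two things are at stake. First, the secondary outcome: the intervention promotes fruit, so achievers lost in this way would be expected more often in the intervention arm, which would shrink the observed difference. Second, the tailoring: because the deficits in Table 1 are alternatives, a participant already at four fruit serves can enrol on another deficit and be sent fruit messages written for someone not yet performing the behaviour.

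The activity item raises a similar but weaker question, because it asks for a daily average while the program goal allows fewer than seven days.

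**Working it through.** The plan gives no figure for stage-of-change. Its one full sample-size calculation is for body weight and has no stage input, so nothing there changes. The check is a comparison of texts with some short arithmetic.

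**Fruit rule against the other rules**

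| Behaviour | Eligibility deficit (Table 1) | Program target | Counted as performing (Secondary outcomes) |
|---|---|---|---|
| Vegetables | below 5 serves/day | 5 serves/day | 5 or more |
| Fruit | below 2 serves/day | 2 serves/day | 2 or 3 only |
| Take-away meals | more than 1/week | 1/week or less | 1/week or less |
| Sugar-sweetened beverages | 1 L/week or more | below 1 L/week | below 1 L/week |

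For three of the four dietary behaviours, performing is exactly the complement of the eligibility deficit. Fruit is the exception: four or more serves is neither a deficit nor a performed behaviour.

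**What happens at four serves.** The highest stage available is preparation. Suppose a participant starts at one serve and plans to eat more within a month (preparation), reaches four serves, and then has no plan to eat still more. That participant is staged as pre-contemplation at follow-up. Another who starts in pre-contemplation and still plans to eat more at follow-up moves up. The direction therefore depends on the intention answers, but action and maintenance are closed to both.

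**Effect on the arm difference.** Let p be the true proportion at two or more serves and m the proportion at four or more, with subscripts I and C for intervention and control.

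- Observed difference = (p_I − m_I) − (p_C − m_C) = (p_I − p_C) − (m_I − m_C).
- If p_I exceeds p_C, the difference is understated when m_I exceeds m_C.
- Its sign changes only if m_I − m_C is larger than p_I − p_C.

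The article gives none of these four proportions.

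**Activity item.** Average minutes per day from 60 minutes on d days a week = 60 × d / 7. Minutes needed on each of those days to average 60 = 420 / d.

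| Days | Average at 60 min/day | Minutes per active day needed |
|---|---|---|
| 4 | 34.3 | 105 |
| 5 | 42.9 | 84 |
| 6 | 51.4 | 70 |

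Someone who just meets the goal on four to six days averages 34 to 51 minutes and has to answer no. Someone who does clearly more on those days can answer yes.

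**The case against.** The strongest reply on fruit is that the program target is two servings, not a minimum of two, and that the scoring rule includes two. The knowledge question in the same section also uses a two-to-three band for fruit, separate from higher bands, so the limit may be deliberate. The article is a condensed account, the questionnaire items come from cited sources, and the live branching may differ. This stands to the extent that reading two as a minimum is an inference. It is well supported, though: the eligibility threshold, the open-ended vegetable rule and the Background all point the same way, and nothing in the article gives a reason for an upper limit.

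It is also fair to say that high consumers are not lost to the trial. Fruit intake is a secondary outcome in its own right, and activity is measured separately by questionnaire. That limits the damage but does not repair the stage outcome.

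On activity, the objection largely succeeds. The item says on average, Table 1 uses below 60 minutes a day, and the program goal itself prefers daily activity. The item also names no intensity, whereas the goal is moderate intensity, so in that respect it is looser than the goal.

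A reader might infer three stronger things that the article does not support:

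- **That anyone active on most but not all days is scored as not performing.** The averaging in the item rules this out.
- **That the arm difference could be reversed.** This needs differential misclassification larger than the true difference, and no figure in the article bears on it.
- **That the bias can be put in percentage points.** If one simply assumed 2–10% of the intervention arm and 1–3% of controls at four or more serves, the distortion would run from 2 − 3 = −1 to 10 − 1 = +9 points. These shares have no source, and even the sign is not fixed.

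**Conclusion.** The fruit point holds. As written, the rule cannot place a participant at four or more serves in action or maintenance, and this misclassifies some achievers on a secondary outcome. Attenuation of the arm difference is the likely direction, on the assumption that high fruit intake becomes more common under the intervention than under control. The size is unknown. The conclusion also assumes that two servings is meant as a minimum and that the survey follows the printed rule.

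The activity point is secondary: the stage item is stricter than the stated goal only for people at or near 60 minutes on four to six days, and it agrees with the eligibility criterion. The net direction of any misclassification there cannot be told.

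The vegetable, take-away and beverage rules are sound. The matter is minor and worth correcting because correction is nearly free.

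**What to change.** 1. **Check the live survey.** Confirm whether it applies the upper limit. If it does not, correct the text only.
2. **Rescore fruit for the outcome analysis.** Count two or more serves a day as performing, from the intake answer recorded before the branching. Compare action and maintenance combined with the earlier stages, for fruit only. This is a dichotomous outcome, so the planned Chi-squared test applies. Keep the full set of stages for the other behaviours. Fix the rule before unblinded analysis.
3. **Correct the branching for new participants.** The Trial status section says recruitment is continuing, so those at four or more serves can still be asked the six-month question. This also corrects the baseline stage used for tailoring their messages.
4. **Reconcile the activity passages.** Either align the stage item with the goal in the TXT2BFiT program section, or state that the stage outcome refers to a daily average of 60 minutes and is stricter than that goal.

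The cost is one scoring rule and a small survey edit; no new data are needed for the rescoring. The downside is that action and maintenance cannot be separated for high fruit consumers already surveyed, because they were not asked how long they had kept it up.
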